## Abstract

**Background:**

Tobacco use adversely affects oral health. Tobacco use prevention and cessation (TUPAC) counselling guidelines recommend that healthcare providers ask about each patient's tobacco use, assess the patient's readiness and willingness to stop, document tobacco use habits, advise the patient to stop, assist and help in quitting, and arrange monitoring of progress at follow-up appointments. Adherence to such guidelines, especially among dental providers, is poor. To improve guideline implementation, it is essential to understand factors influencing it and find effective ways to influence those factors. The aim of the present study protocol is to introduce a theory-based approach to diagnose implementation difficulties of TUPAC counselling guidelines among dental providers.

**Methods:**

Theories of behaviour change have been used to identify key theoretical domains relevant to the behaviours of healthcare providers involved in implementing clinical guidelines. These theoretical domains will inform the development of a questionnaire aimed at assessing the implementation of the TUPAC counselling guidelines among Finnish municipal dental providers. Specific items will be drawn from the guidelines and the literature on TUPAC studies. After identifying potential implementation difficulties, we will design two interventions using theories of behaviour change to link them with relevant behaviour change techniques aiming to improve guideline adherence. For assessing the implementation of TUPAC guidelines, the electronic dental record audit and self-reported questionnaires will be used.

**Discussion:**

To improve guideline adherence, the theoretical-domains approach could provide a comprehensive basis for assessing implementation difficulties, as well as designing and evaluating interventions. After having identified implementation difficulties, we will design and test two interventions to enhance TUPAC guideline adherence. Using the cluster randomised controlled design, we aim to provide further evidence on intervention effects, as well as on the validity and feasibility of the theoretical-domain approach. The empirical data collected within this trial will be useful in testing whether this theoretical-domain approach can improve our understanding of the implementation of TUPAC guidelines among dental providers.

**Trial registration:**

Current Controlled Trials ISRCTN15427433

## Background

### Tobacco use prevention and cessation counselling among dental providers

Globally, tobacco use remains the leading preventable risk factor for premature morbidity and mortality [1]. Tobacco use is harmful to all human biological systems, including the oral cavity. It is a major contributor to oral cancer and periodontal diseases and is a significant risk factor for failed dental implant therapy [2-4]. Other effects relevant to dentistry are staining and discolouration of teeth and dental restorations, as well as congenital defects such as oral clefts if expectant mothers smoke [4-6]. Conversely, tobacco use cessation has positive immediate and long-term effects; smell and taste return to normal within one month after cessation, while the risk for oral cancer, for example, decreases to nearly the same level as for never-users during the following years [2,4].

In Finland, primary healthcare is provided by municipal health centres under the Primary Health Act. This also includes free or financially subsidised dental care. Health promotion and prevention are the main responsibilities of health centres and are becoming increasingly important as healthcare costs are growing. Currently, the Finnish government and municipal administrations are working to develop health centres' operations towards more cost-effective practices (The Government Resolution on the Health 2015 public health programme, http://pre20031103.stm.fi/english/eho/publicat/health2015/health2015.pdf). To improve the quality of care, as well as the cost-effectiveness of primary care, healthcare professionals should be better supported in implementing clinical guidelines and preventive services.

Annually, more than one-third of Finnish residents visit a dental practitioner in health centres, with an average of 2.6 appointments per year [7]. This gives an excellent opportunity for dental providers to make a high public health impact, for example, in tobacco cessation. The fact that over 80% of tobacco users are worried about the health effects of smoking and some 60% would like to give it up [8] shows the potential for dental providers to contribute to tobacco use prevention and cessation (TUPAC) counselling. Besides cessation, promoting tobacco abstinence is particularly important among young people who are likely to take up tobacco use. In Finland, dental providers in health centres meet about 75% of the population of minors (<18 years) each year [7], more than other healthcare professionals. This opportunity has been recognised by the World Health Organization (WHO) Global Oral Health Programme, the European Union (EU) Working Group on Tobacco and Oral Health, and recently by the European Workshop on Tobacco Use Prevention and Cessation for Oral Health Professionals [9-11]. The primary message is that oral health professionals should strengthen their contributions to tobacco cessation programmes so that all patients who use tobacco are counselled to quit.

### Guidelines on tobacco dependency treatments

The Finnish Medical Society Duodecim produces national Current Care guidelines based on up-to-date evidence to support healthcare decision making in Finland. The guideline for Smoking, Nicotine Addiction, and Interventions for Cessation was published for the first time in 2002 and updated in 2006. The Current Care guidelines for TUPAC counselling recommend a six *A*s approach (Ask, Assess, Account, Advise, Assist, Arrange) [12], which is similar to the five *A*s approach presented by US and other national guidelines [13]. The main principles in TUPAC guidelines include a recommendation that the healthcare provider ask about each patient's tobacco use at least once a year, assess the patient's readiness and willingness to stop, document tobacco use habits (what type of tobacco, quantity, duration), advise the patient to stop tobacco use and instigate supportive measures where necessary, assist and help the patient in his/her attempt to stop tobacco use, and arrange monitoring of progress at follow-up appointments. Historically, however, dental providers, and dentists in particular, have not been routinely involved in the TUPAC counselling. The latest national data show that only 10.5% of daily tobacco users who had visited a dentist during the past year had received advice to quit tobacco use [8]. The gap between guideline recommendation and implementation is evident.

### Developing interventions to enhance guideline implementation

The challenges in designing interventions to increase healthcare providers' effective implementation of clinical guidelines are many. Although the implementation depends on behaviour change, much of the current research investigating methods of increasing guideline implementation does not draw on theories of behaviour change. The UK's Medical Research Council (MRC) has produced guidance for designing and evaluating interventions that emphasises the importance of applying theory to the early phases of intervention development [14]. Examples of such theories are the Theory of Planned Behaviour [15], Social Cognitive Theory [16], and Theory of Interpersonal Behaviour [17]. Since many theories exist, it is often unclear which theory to use in addressing an implementation problem. To simplify the selection of theory, a consensus group of health psychologists and implementation researchers identified 12 theoretical domains from 33 theories of behaviour change that could be used to investigate the implementation of clinical guidelines [18]. These are knowledge; skills; professional role and identity; beliefs about capabilities; beliefs about consequences; motivation and goals; memory, attention, and decision processes; environmental context and resources; social influences; emotion; behaviour regulation; and nature of behaviours. This theoretical-domains framework provides a comprehensive basis for assessing problems and will serve as the first key step in our study to evaluate implementation difficulties of TUPAC guidelines among dental providers.

To progress from a theoretical assessment of the implementation problem to intervention design, Michie *et al. *have proposed a list of behaviour-change techniques to target each of the theoretical domains [19], examples of which are shown in Figure 1. For example, if the domain motivation and goals needs improvement, behaviour-change techniques such as rewards, graded tasks, and motivational interviewing would be suitable intervention components. If beliefs about consequences need changing, providing information regarding intervention outcomes could be used. Thus, the theoretical framework can guide the selection of behaviour-change techniques in enhancing guideline adherence among healthcare providers.

**Figure 1 F1:**
[figure not shown]
**Steps for modelling intervention (modified from Medical Research Council framework) **[14].

### Aims and objectives

The general aim is to enhance implementation of TUPAC counselling guidelines among dental providers. The first objective is to develop a theoretically informed measure for assessing the implementation difficulties among dental providers related to TUPAC counselling guidelines (six *A*s approach) using a theory-based assessment and to apply it to a sample of Finnish dental providers. After identifying implementation difficulties, our second objective is to design two interventions to enhance guideline adherence using relevant behaviour-change theories and intervention techniques. Finally, we aim to conduct a cluster randomised controlled trial to assess intervention effects. A cluster design will be used to reduce contamination across participants.

The theoretical and chronological framework of the study is provided in Figure 1.

## Methods

### Participants

All dentists and dental hygienists employed by the Finnish municipal health centres of Vaasa (9 clinics) and Tampere (28 clinics) will be invited to participate, except two clinics' staff in Tampere (emergency and special treatment clinic) and one clinic's staff in Vaasa (undergraduate education clinic) (Figure 2). Implementing TUPAC counselling interventions in those excluded clinics would not be feasible. Participants meeting the inclusion criteria will receive the explanatory statement of the study (additional files 1 and 2), consent form (additional file 3), and instructions to participate (additional file 4). The survey will be conducted using either a web-based survey http://www.surveymonkey.com or a more traditional paper form survey. Strategies to promote response rates among dental providers include offering two movie tickets (value about €10 per ticket) for participation. We will also send two reminder letters (the first reminder one week and the second two weeks after the first request to respond) to nonrespondents.

**Figure 2 F2:**
[figure not shown]
**Potential flowchart of participants and clusters in OH NO TOBACCO! trial**.

### Primary outcome measures

The meta-analysis shows that if TUPAC guidelines are implemented, the time used by healthcare providers for counselling is one of the best predictors for counselling success [13]. As our target behaviour will be the implementation of TUPAC guidelines, our primary outcome measures will be (a) whether the TUPAC guideline recommendations are implemented, and (b) if implemented, the estimated time used for the counselling. We will use the electronic dental record (EDR) audit for measuring these outcomes. If the dentist or dental hygienist provides TUPAC counselling, documented procedure codes will give information on the effect counselling may have had. A similar procedure-code documenting system is widely used in dentistry (fillings, extractions, etc.). The codes for TUPAC counselling will be as follows: TI02 = minimal counselling (<3 minutes), TI03 = low-intensity counselling (3 to 10 minutes), and TI04 = higher-intensity counselling (>10 minutes). Categories of intervention duration are based on the meta-analysis, where the estimated odds ratios (ORs) for TUPAC counselling are reported using the same counselling durations (OR = 1.3 for minimal counselling, OR = 1.6 for low-intensity counselling, and OR = 2.3 for higher-intensity counselling) [13]. When multiplying the procedure codes by the estimated ORs and summing the results, we will create one continuous primary outcome. The EDR softwares used in the Vaasa and Tampere health centres are identical (Effica by Tieto Finland, Helsinki) and include the above-mentioned codes for each intervention intensity.

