### Sample size

There is a scarcity of recent national data regarding the implementation of TUPAC counselling guidelines reported by dental providers. Hence, we conducted our sample size calculations based on population reports collected by the National Institute for Health and Welfare from a random sample (n = 5,000) of Finnish adults [8]. The data showed that 10.5% of surveyed tobacco users who visited the dentist at least once during the past 12 months had received any TUPAC counselling [8]. As our primary aim is to compare the implementation of TUPAC counselling guidelines between control versus two intervention groups, sample size is calculated using the following assumptions: Our aim is to increase the proportion of counselled patients from 10.5% (control) to 33% in the first (low-intensity) intervention group and to 63% in the second (high-intensity) intervention group, as validated by dental record audit. To achieve 80% power, with a two-sided 5% significance level with an estimated intra-class correlation of 0.02, we will need totally 72 participants and 12 clusters with an average of six participants per cluster. Assuming a baseline response rate of 76%, we will need a sample of 95 dental providers.

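### The plan leaves unclear whether counselling time among counselled patients is a primary outcome in its own right; if it is compared between arms, that comparison is not randomised

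*Protocol article*

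**What the plan says.** All references are to the Protocol article.

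- Primary outcome measures, opening: two primary measures are listed. The first, (a), is implementation of the guideline. The second is "b) if implemented, the estimated time used for the counselling". Both are to be measured by the audit of electronic dental records.
- Same section, the codes: "TI02 = minimal counselling (<3 minutes), TI03 = low-intensity counselling (3 to 10 minutes), and TI04 = higher-intensity counselling (>10 minutes". Their weights are "OR = 1.3 for minimal counselling, OR = 1.6 for low-intensity counselling, and OR = 2.3 for higher-intensity counselling".
- Same section, end: "When multiplying the procedure codes by the estimated ORs and summing the results, we will create one continuous primary outcome".
- Sample size, the target for the three arms: "increase the proportion of counselled patients from 10.5% (control) to 33% in the first (low-intensity) intervention group and to 63% in the second (high-intensity". This corresponds to measure (a). No planning figure is given for (b) or for the weighted sum.
- Data analysis: adjusted generalised linear models and modified t-tests, at cluster and individual level, under intention-to-treat principles. No analysis restricted to counselled patients is described.
- Discussion, limitations: the trial's primary outcomes are again mentioned in the plural.

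**The concern.** There are three candidates for the primary endpoint: the pair (a) and (b), the single weighted score, and the proportion counselled that drives the sample size. The article does not say which governs, or how (a) and (b) relate to the score. The definition of the primary outcome should not be left open in this way.

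The gap matters because of how (b) is defined. Counselling time exists only for a patient who was counselled. Being counselled happens after randomisation and is what the interventions are designed to change. The counselled patients in the three arms would therefore be differently selected groups, and randomisation would not protect a comparison of their counselling time. If (b) were reported as a primary result, (a) and (b) could point in opposite directions although no patient received less counselling.

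**Working it through.** **What there is to reproduce.** The plan gives no figure for (b) or for the score. Its sample size concerns the proportion counselled only and is not examined here.

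**Inputs from the plan.** Proportion counselled p: 0.105 (control), 0.33 (low intensity), 0.63 (high intensity). Weights: 1.3, 1.6 and 2.3 for TI02, TI03 and TI04.

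**Inputs assumed.** Minutes per patient and the mix of codes; the documents give neither. Patients who would be counselled without an intervention (10.5%) are also counselled in the intervention arms.

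**Step 1: time among the counselled and time per patient seen.** Let *base* be the time for patients counselled anyway and *added* the time for newly counselled patients.

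- Mean among the counselled = (0.105 × base + (p − 0.105) × added) / p
- Mean per patient seen = p × that value

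With base 12 and added 2:

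- Control: 12 among the counselled; 0.105 × 12 = 1.26 per patient seen.
- Low: (1.26 + 0.225 × 2) / 0.33 = 1.71 / 0.33 = 5.2; 1.71 per patient seen.
- High: (1.26 + 0.525 × 2) / 0.63 = 2.31 / 0.63 = 3.7; 2.31 per patient seen.

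With base 6 and added 2: 6, 3.3 and 2.7 among the counselled, against 0.63, 1.08 and 1.68 per patient seen.

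**Step 2: what drives the direction.** Rearranged, the shift in (b) is (p − 0.105)/p × (added − base). The first factor is the share of counselled patients who are newly counselled: 0.225/0.33 = 68% in the low arm and 0.525/0.63 = 83% in the high arm. The sign depends only on whether added counselling is shorter or longer than existing counselling.

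**Step 3: the same check on the plan's codes and weights, per 1,000 patients.** Assume 1.5, 6.5 and 12 minutes for the three codes, and 35 patients in each code in control.

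- Control: 35 × (1.5 + 6.5 + 12) / 105 = 700 / 105 = 6.67 minutes among the counselled; score 35 × (1.3 + 1.6 + 2.3) = 182.
- Low, with 225 added patients all TI02: (700 + 337.5) / 330 = 3.14 minutes; score 182 + 292.5 = 474.5.
- High, with 525 added patients all TI02: (700 + 787.5) / 630 = 2.36 minutes; score 182 + 682.5 = 864.5.

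Other assumed mixes for the added patients, with the 105 patients counselled anyway unchanged:

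| Added mix TI02/TI03/TI04 (%) | Minutes among counselled, low | high | Score, low | high |
|---|---|---|---|---|
| 100/0/0 | 3.14 | 2.36 | 474.5 | 864.5 |
| 80/20/0 | 3.83 | 3.19 | 488 | 896 |
| 60/30/10 | 4.88 | 4.49 | 517.25 | 964.25 |
| same as control | 6.67 | 6.67 | 572 | 1092 |
| 20/30/50 | 7.75 | 7.99 | 607.25 | 1174.25 |

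The control values for comparison are 6.67 minutes and a score of 182. Now let the 105 move up one category (those in TI04 staying there, giving 0/35/70) with all added patients in TI02. Time among the counselled still falls, to 1405/330 = 4.26 and 1855/630 = 2.94, while the score rises to 509.5 and 899.5.

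Time among the counselled can thus fall, stay level or rise. The score rises in every row, because uncounselled patients stay in the comparison with a contribution of zero.

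**The case against.** The strongest reply is that the plan never says (b) will be tested within the counselled. A reader might infer such a test from the list of primary measures, but Data analysis describes none, and the words of condition may only reflect that an uncounselled patient has no counselling time. The section can be read as one sequence: two aspects of interest, one audit, three codes, one score. On that reading (a) and (b) are components of the score, and there is neither a biased comparison nor a strict contradiction. This much stands: the only variable the plan says it will construct is unconditional and moves the right way in the check above.

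Two further points also stand. The minutes and mixes are assumptions, and nothing in the article says added counselling will be brief, so a predicted appearance of harm is not supported. And the trial's participants are providers, so the individual level may mean the provider; the patient-level figures illustrate the mechanism and do not reproduce a stated analysis.

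What does not stand is that this is detail a condensed article may leave out. The article does state its primary outcomes, in the plural and in the singular, and sizes the trial on one of them. Nothing in it rules out (b) being reported as a primary result.

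**Conclusion.** The concern holds in a limited, conditional form. The article is inconsistent about its primary endpoint and does not say whether (a) and (b) are tested or only feed the score. If (b) is compared between arms as listed, the comparison is not randomised whatever the code mix. In the illustrations, where added counselling is all brief and existing counselling is unchanged, time among the counselled falls by roughly half or more in both intervention arms (12 to 5.2 and 3.7 minutes, or 6.67 to 3.14 and 2.36), with no patient receiving less. With a longer mix it rises instead. The proportions and weights are the plan's; the minutes and mixes are assumed. The documents do not support the stronger claims that the plan will make this comparison or that it will show harm.

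**What to change.** State that the weighted score, computed over all patients seen and counting zero for a patient without a TI02, TI03 or TI04 code, is the sole primary outcome. Make (a) supportive. Replace (b) with counselling time per patient seen, zero if none, also supportive; because the codes record time bands, state in advance the minutes assigned to each. Report the code mix among counselled patients as description, without a test between arms.

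The cost is small: a change of wording and a count of patients seen from the same record audit, with no new data from providers. Time among the counselled loses its primary status.

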### Data analysis

We will follow intention-to-treat principles at both individual and cluster levels. Participants will be assigned to the cluster they were in when the trial began. However, if a participant moves to another cluster during the trial period that is assigned to a higher intervention arm, they will be shifted to that cluster.

In data analysis, we will first analyse descriptive variables to explore the distribution of background data using chi-square and *t*-tests. To compare intervention effects between control and intervention groups, we will use adjusted, generalised linear models and modified *t*-tests, taking into account the effect size. Analyses will be conducted at the cluster and individual level, and all estimates will be presented with standard deviations or 95% confidence intervals.

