### Trial update

The baseline survey (background information, self-reported guideline implementation, the theory-based assessment of implementation difficulties) and the EDR audit of the sample were conducted in September 2009. Of those eligible, 76.8% participated (n = 73/95). The study participants were fairly representative of municipal dental providers (Table 1). Participating dentists had practiced more clinical years on average (22.4 years) compared to dental hygienists (10.2 years; *p *< .001) and reported higher lifetime tobacco abstinence (72.2%) than dental hygienists (21.1%; *p *< .001) (Table 2). Regular tobacco use was uncommon in both provider groups. More dental hygienists had received undergraduate education on TUPAC counselling compared to dentists (84.2% versus 24.1%; *p *< .001). The results of the self-reported guideline implementation, theory-based assessment of implementation difficulties, and EDR audit will be reported elsewhere.

**Table 1 T1:** The comparison of gender and mean age of study participants, nonrespondents, and municipal dental practitioners in Finland

	Participants		Nonrespondents		Total		Municipal dentists
	Dentists (n = 54)	Hygienists (n = 19)	Dentists (n = 19)	Hygienists (n = 3)	Dentists (n = 73)	Hygienists (n = 22)	Dentists* (n = 2,002)
Female (%)	81.5	100	68.4	100	78.1	100	77.4
Mean age, years (SD)	48.7 (9.1)	37.3 (9.5)	51.1 (9.3)	46.7 (16.7)	48.9 (9.5)	38.6 (10.7)	49.5 (8.7)

*Finnish Dental Association statistics 2010. No national data available for dental hygienists.

**Table 2 T2:** Participant characteristics at baseline

	Dentists (n = 54)	Dental hygienists (n = 19)	*p *value*	Total (n = 73)
Response rate (%)	74.0	86.4	.27	76.8
Years practised (SD)	22.4 (9.1)	10.2 (7.6)	<.001	19.2 (10.2)
Mean clinical hours per week (SD)	28.0 (7.4)	31.1 (8.2.)	.14	28.8 (7.7)
Tobacco use (%)				
Never	72.2	21.1	<.001	58.9
Gave up 1 to 12 months ago	3.7	0	.40	2.7
Occasional	1.9	10.5	.10	4.1
Regular	3.7	5.3	.71	4.1
Received undergraduate education on tobacco use prevention or cessation counselling (%)	24.1	84.2	<.001	39.7
Received continuing education on tobacco use prevention or cessation counselling (%)	37.0	31.6	.67	35.6

**p *values calculated using chi-square and *t*-tests.

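### The primary score is a sum of weighted counselling codes with no patient or time denominator, so it measures counselling volume and not adherence, and does not match the proportion that the trial aims to change

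*Protocol article*

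**What the plan says.** Under Primary outcome measures, the target is guideline implementation, in two parts: "a) whether the TUPAC guideline recommendations are implemented, and (b) if implemented, the estimated time used for the counselling". Both come from an audit of electronic dental records, using three procedure codes graded by counselling time. Each code has a weight from a meta-analysis: "OR = 1.3 for minimal counselling, OR = 1.6 for low-intensity counselling, and OR = 2.3 for higher-intensity counselling". The score is then formed: "When multiplying the procedure codes by the estimated ORs and summing the results, we will create one continuous primary outcome". That section gives no divisor, audit window or unit of summation.

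The Sample size section states the goal differently: "Our aim is to increase the proportion of counselled patients from 10.5% (control) to 33% in the first (low-intensity) intervention group". For the other active arm the target is 63%, and the record audit is meant to confirm these proportions. The 10.5% comes from a population survey of tobacco users who had visited a dentist in the past year.

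The Data analysis section plans adjusted generalised linear models and modified t-tests, and says "Analyses will be conducted at the cluster and individual level". It names no exposure term or workload covariate. Table 2, under Trial update, reports weekly clinical hours of 28.8 (SD 7.7) for all 73 participants.

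**The concern.** Adherence is a per-patient idea here. The guideline, as described in the Background, asks about every patient's tobacco use at least yearly, and the trial's goal is a share of patients. A sum of weighted codes has no exposure in it. Of two providers who counsel the same share of patients equally intensively, the one with twice the patients scores double. This remains true even if each patient is coded only once.

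Two things are at stake. First, the main result could not be read as adherence, nor set against the 10.5%, 33% and 63% that the plan uses, although both quantities come from the same record audit. Second, differences in workload between providers add variance to the score that has nothing to do with adherence.

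**Working it through.** The plan gives no expected value or SD for the score, so there is no figure for it to reproduce. The sample size of 72 is used below only to obtain 24 providers per arm, assuming three equal arms.

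**Inputs**
- Weights 1.3, 1.6 and 2.3 (Primary outcome measures).
- Hours 28.8, SD 7.7 (Table 2), so the CV of hours is h = 7.7/28.8 = 0.267.
- Assumed: patients seen are proportional to hours, and hours are independent of adherence and of cluster.

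**1. Two providers with identical adherence**
- Hours at plus and minus 1 SD: 28.8 + 7.7 = 36.5 and 28.8 − 7.7 = 21.1.
- For illustration, assume one patient per hour, 20% counselled and an equal mix of codes. The mean weight is (1.3 + 1.6 + 2.3)/3 = 1.733.
- Weekly score: 36.5 × 0.20 × 1.733 = 12.65 against 21.1 × 0.20 × 1.733 = 7.31. The ratio is 36.5/21.1 = 1.73 and does not depend on these illustrative values.
- Divided by patients seen, both providers score 0.20 × 1.733 = 0.347.
- With the same code mix, a 21.1-hour provider who counsels 33% ties with a 36.5-hour provider who counsels 33% × 21.1/36.5 = 19%.

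**2. Extra variance**

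Let c be the CV of the score per hour, which the article does not give. For a product of independent quantities, the squared CV of the total divided by that of the rate is [(1 + c²)(1 + h²) − 1]/c² = 1 + h² + h²/c², with h² = 0.0715.

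| Assumed c | Variance ratio | Equivalent loss of participants (1 − 1/ratio) |
|---|---|---|
| 0.5 | 1.36 | 26% |
| 1.0 | 1.14 | 13% |
| 2.0 | 1.09 | 8% |

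**3. Chance difference between arms from hours alone**
- SE of the difference in mean hours: 7.7 × √(2/24) = 2.22 h, which is 2.22/28.8 = 7.7% of the mean.
- 1.96 × 7.7% = 15.1%. A simulation with independent normal hours gave a 95% range of 0.86 to 1.16 for the ratio of arm mean scores at equal adherence.
- If hours were alike within clinics, this range would be wider.

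**The case against.** The sentence defining the score is condensed, and the full protocol or analysis plan may add scaling. The planned adjusted models could carry an exposure term, and both weekly hours and a baseline record audit are available. A proportion to be validated by the audit also suggests that a patient denominator can be obtained. This stands as a reason to expect an easy repair. It does not change the stated rule, which is a positive definition of the outcome as a sum. Adding a workload covariate to a model for a sum would recover some precision but would not turn the sum into a measure of adherence.

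Three stronger readings are tempting and are not supported.

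- **Bias or false positives.** A reader might infer that workload biases the comparison. Clusters are randomised, so workload balances in expectation, and a valid test already allows for the 15% chance range. That range is also small beside the planned increases of 33/10.5 = 3.1-fold and 63/10.5 = 6-fold. Systematic bias would need workload, leaving or movement to differ by arm, and the article does not show this.
- **Cluster size.** A reader might infer that larger clusters score higher. That follows only if scores are summed over a cluster. With provider-level scores or cluster means it does not, and the article leaves the unit open.
- **Leavers.** A reader might infer that early leaving lowers scores. That holds only if absence or leaving falls within the audit window. The article gives neither the window nor any data on leavers.

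The objection that the power cost rests on an assumed CV is also fair. At a CV of 2.0 it falls to about 8%. A sum can be a legitimate measure of total counselling delivered, but that is not the aim stated here.

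**Conclusion.** The point holds as one of construct validity and precision. As defined, the primary score is a volume measure. It does not match the proportion of counselled patients in the Sample size section, and this mismatch rests on the text alone.

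The sizes rest on assumptions. The 1.73-fold difference between providers at plus and minus 1 SD of hours assumes that patients seen scale with hours. The extra variance of about 14% to 36% further assumes a CV of 1.0 to 0.5 for the score per hour and independence of hours and adherence. A larger CV makes it smaller. No bias in the arm comparison has been shown.

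**What to change.** In Primary outcome measures, define the score as the provider's weighted sum divided by the number of patients that provider treated in a fixed, stated audit window, taken from the same record extract. If the records identify tobacco users, dividing by recorded tobacco users would match the population behind the 10.5% benchmark more closely. For cluster-level analysis, use total score divided by total patients.

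Alternatively, keep the sum and analyse it in a log-link count-type model with log(patients treated) as offset. The two approaches are not identical. Averaging per-provider ratios counts every provider equally, however few patients they saw, while the offset model weights providers by exposure. Choose one before follow-up data are analysed.

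The Sample size section should then be aligned. If each counselled patient is coded once, the score per patient is the share counselled times the mean weight, so it still is not itself the 10.5%, 33% or 63%. Reporting the unweighted share beside it would close that gap.

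The cost is one more field in an extract already planned, one or two sentences in the outcome definition, and a rate that must be explained to readers.
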